### Trial sample size and power

The sample size estimates accounts for the expected dependency of variables [22]. This family based RCT with 740 families (370 in each arm) of at least two participants each (minimum of 1480 enrolled participants) and no more than 15% loss to follow-up after 2 years will have 90% power to detect an estimated 10% difference in the proportion of participants at 3 or more CHD risk factor goals, the primary effectiveness endpoint of this trial (55% in the intervention group as compared to the expected rate of 45% in the control group). The baseline rate of the composite primary outcome in a large cluster randomized trial in India [17] is used as the expected rate in the control group (data not published) and the lower limit of 95% confidence interval of the improvement in the same composite outcome in a demonstration project in India [13] is used to estimate the rate in the intervention group (data not published). This is for a two sided test with an alpha of 0.05 and a rho or intra-cluster correlation coefficient (ICC) of 0.20. The ICC of the composite primary outcome is also estimated from the baseline data of the above mentioned cluster randomized trial [17]. The power in this study is more than 80% for all secondary endpoints of interest including the change in risk scores.

### Participating centres

The study will be conducted in Kerala with active support from Sree Chitra Tirunal Institute of Medical Sciences and Technology (SCTIMST) in Trivandrum in India. In total, 3716 patients with premature (<55 years) non-fatal acute coronary syndrome were registered in this hospital in the last ten years. The average number of cases per year in this center is in the range of 300–500. Nearly 500 patients are registered in the last one year alone. We will invite 740 such families in this trial and the recruitment will involve both prospective cases as well as cases in the last 1 year. The medical records will be used to confirm the diagnosis of CHD and the eligibility criteria (Age < 55 years).

### Data entry and data management

Trained and certified project staff will collect data using study questionnaires. They will also be trained in collection of clinical data from health records and/or personal information. The project staff under the supervision of a post-doctoral fellow and the principal investigator will complete data entry on a specially designed tablet computer based data application. The data application has been developed on My SQL 7.0 server. The application will upload the data directly on a cloud server. The data will be collated, cleaned, queries resolved and analysed centrally. All entries in the tablet application will be double checked by the post-doctoral fellow using a specially designed data review application. The application also allows the user to send queries directly back to the field staff for their review and action. Further, the accuracy of data entry in randomly selected fields (10% of the general fields and all anthropometric, BP, and biochemistry data) will be checked independently by the study principal investigator.

The study will collect various type of research data including both quantitative and qualitative data. Data will be generated from focus groups, in-depth semi-structured interviews, medical records, questionnaires, clinical and anthropometric measurements and blood biochemistry. All data will be de-identified to ensure confidentiality of information.

Long-term data storage: Upon completion of data collection and entry, data packets will be created containing the following: a final STATA data file; a read me file describing data collection, entry, auditing, and cleaning; a data dictionary with detailed description of study variables, and an annotated PDF of questionnaires and laboratory data with variables and coding noted. De-identified study data will be maintained indefinitely at the secured data servers of the study sponsor. Periodically, the data will be checked to ensure long-term integrity of the datasets. A master list linking study identifiers with individuals will be maintained for five years to allow the researchers to reach individuals if needed to inform them of individual study results that could impact their health. After five years the linkage file will be destroyed. Three years after the completion of the study, study data (de-identified quantitative data including survey and data from clinical records and qualitative data comprising de-identified transcripts) for all participants who consent to having their data made public will be made available to other researchers. Information on the study will be available on the website of the sponsor as well as reported in scientific journals and at scientific conferences. In addition, the study results will be included in clinicaltrials.gov. Interested collaborators can contact the study PI to discuss the possibility of data usage.

### Data analysis plan

All quantitative analyses (for Aim 2) will follow recommended intention to treat guidelines for RCT. A generalizing estimating equations (GEE) framework for clustered data [23] will be used to assess the statistical significance of any observed intervention effect on the primary endpoint. In this analysis, the dependent variable will be the indicator for whether the study participant is at three or more CVD risk factor reduction goals at the end of 12 and 24 months follow-up period, minus the observed probability of this endpoint in the absence of an intervention (rate in control group). An exchangeable working correlation matrix will be used to incorporate the clustering within the families, with a log link and binomial variance specified. The exponentiated point and interval estimates from the intercept of this model will quantify the intervention effect. A similar GEE approach will be used to estimate and test the significance of intervention effects on secondary endpoints. For continuous markers, such as SBP, FPG, HbA1c and LDL, the within-participant difference will serve as the dependent variable in a GEE model as above, with the identity link function and the distribution specified as normal. To assess the causal effect of the intervention adjusted for bias due to non-adherence and loss to follow up, marginal structural models will be fit, embedded around the analysis approaches outlined above [24].

All qualitative data, including that collected for Aim 1 and Aim 3, will comprise the verbatim transcripts of the audio recordings from all focus group discussions and interviews. Audiotapes of focus group discussions/interviews will be transcribed, de-identified, and the transcriptions audited for accuracy. Using ATLAS.ti software to manage the data, analyses of the textual data will follow the thematic analysis (e.g., for suggestions from patients and care givers for the intervention). Key themes will be identified from the data (inductively) and from the discussion guides (deductively), and these themes will be compared using structured comparisons to identify specific issues relevant to sub-groups of participants.

To compare the cost-utility of the intervention to standard arm management, we propose to calculate an incremental cost/utility ratio [net costs to net utility: costs of intervention – costs of control/utility of intervention – utility of control]. To calculate utility, we will use 12-monthly health utility. The chosen measure of utility will be the closest option to a global measure, the quality adjusted life year (QALY], and is calculated as the sum of mean survival time [life years] x utility scores at 12 and 24 months [25]. Both 12 and 24-month costs per QALY will be reported. If the intervention is successful, the modeled long-term cost-utility of the intervention and usual care will be compared using Markov Chain Monte Carlo estimation techniques, controlling for age, gender, and risk factor prevalence under different plausible scenarios for how these may evolve over time [26]. Then it will be compared to reference points from the literature – e.g., ceiling ratios for costs per QALY that are less than three times gross domestic product (GDP) per capita [27, 28] that are considered cost-effective [29] (India’s 2013 GDP per capita was $3990; threshold: ≤$11,100 per QALY).

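### The primary GEE model is internally incoherent: a control-centred 0/1 outcome on a log link, with the effect read from the intercept, is undefined at the null and names no arm contrast

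*Protocol article*

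**What the plan says.** The Data analysis plan in the protocol article makes four choices for the primary endpoint:

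- Response: "the dependent variable will be the indicator for whether the study participant is at three or more CVD risk factor reduction goals", assessed at 12 and 24 months, "minus the observed probability of this endpoint in the absence of an intervention (rate in control group").
- Link, variance and clustering: "An exchangeable working correlation matrix will be used to incorporate the clustering within the families, with a log link and binomial variance specified".
- Effect measure: "The exponentiated point and interval estimates from the intercept of this model will quantify the intervention effect".
- Covariates: none are listed. No randomised-arm term is named, and the text does not say whether control participants enter the model.

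This GEE is the only test given for the primary endpoint; the marginal structural models are built around it. Secondary endpoints get a similar approach. Continuous markers have their own response (within-participant change), an identity link and a normal distribution.

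The section Trial sample size and power describes an ordinary two-arm comparison. It assumes 370 families per arm with two or more members apiece and at most 15% lost over two years, and it states that the trial "will have 90% power to detect an estimated 10% difference in the proportion of participants at 3 or more CHD risk factor goals": 55% against 45%, two-sided alpha 0.05, ICC 0.20.

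**The concern.** Each component is familiar, but they do not belong to one model. A log link with binomial variance suits a 0/1 response. Subtracting the control rate turns that response into a residual centred on zero under no effect. An intercept measures a between-arm contrast only if the model is arranged so that it does, and the text does not arrange this. The observed control rate is itself an estimate from randomised, family-clustered participants, yet it enters the response as a number.

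At stake is the test on which the trial's conclusion rests. An analyst who follows the text may get no finite estimate, an interval that cannot express no effect, or a p-value for a null that nobody wants to test. An analyst who repairs it informally must choose among readings that give different estimands. The most natural of them do not hold the 5% level.

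**Working it through.** **Inputs.** From Trial sample size and power: 370 families per arm, at least two members each, loss of no more than 15%, rates 55% and 45%, alpha 0.05 two-sided, power 90%, ICC 0.20. From Data analysis plan: response, link, variance and effect parameter as above. Assumed: exactly two members per family and exactly 15% loss, so 740 × 0.85 = 629 followed per arm.

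**1. The plan's own figure.** The two-proportion formula (pooled variance, no continuity correction) gives 524 per arm. The design effect is 1 + (2 − 1) × 0.20 = 1.2. Then 524 × 1.2 = 628.8, and 628.8 / 0.85 = 740 participants, or 370 families per arm. The stated size reproduces as a two-arm comparison that counts both arms' variance.

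**2. The literal model.** Write pT and pC for the arm rates.
- With pC = 0.45 the response is +0.55 or −0.45.
- In the intervention arm its mean is μ = pT − pC, so the intercept is log(pT − pC). At pT = pC this is log(0), which is undefined.
- Testing intercept = 0 tests μ = 1, a risk difference of 100 percentage points.
- exp(intercept) is always positive, so its interval excludes zero difference and harm whatever the data show.
- At μ = 0.10 the binomial variance is 0.10 × 0.90 = 0.09, while the response's variance is 0.55 × 0.45 = 0.2475.

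**3. What exp(intercept) estimates at 55% v 45%.**
- Intervention arm only: 0.55 − 0.45 = 0.10, the risk difference.
- Both arms: 0.10 / 2 = 0.05, because the control residuals average zero.
- Control rate as a log offset (not in the text): 0.55 / 0.45 = 1.22, the risk ratio.

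One simulated trial shows this. The literal fit gave 0.083 (95% interval 0.049 to 0.141) on the intervention arm and 0.041 on both arms. A GEE with an arm term gave a risk ratio of 1.19 (1.04 to 1.35). A reader expecting a ratio could take 0.083 for a large adverse effect when it is an 8-point benefit.

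**4. Standard error if the control rate is taken as known.**
- One arm: √(0.55 × 0.45 × 1.2 / 629) = 0.0217.
- Difference of two arms: √2 × 0.0217 = 0.0307.
- Type I error using the first: 2 × [1 − Φ(1.96 / √2)] = 2 × [1 − Φ(1.386)] = 16.6%.

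The √2 needs only equal variance in the two arms, which holds at the null with equal allocation. Family size, loss and ICC set the absolute standard errors. The calculation applies to the intervention-only and offset readings. It does not apply to the both-arms reading, whose faults are the halved estimate and the log scale.

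**5. Simulation** (20,000 trials, 314 families of two per arm, ICC 0.20).
- Literal model under the null: mean at or below 0, hence no finite intercept, in 51% of trials.
- Difference tested against zero with the control rate fixed: type I error 16.9%, against 5.3% when control-arm variance is counted.
- Offset reading with the control rate fixed: type I error 17.0%; coverage of the 95% interval 83% under the null and 79% at 55% v 45%.

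**6. Ordinary two-arm comparison.** With the untransformed indicator and both arms' clustered variance, type I error is about 5%, coverage about 95% and power about 90%. As a check, 0.10 / 0.0307 − 1.96 = 1.30, and Φ(1.30) = 90%. This agrees with the power statement.

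**The case against.** The best defence is that the authors plainly meant a two-arm comparison. The power calculation is one, the section commits to intention to treat, and the text never lists the covariates. If the control rate is read as a log offset, the log link, the exponentiation and the intercept all fit together. Intercept = 0 then means a risk ratio of 1, and the undefined null and the 100-point null both disappear. Failure at a non-positive mean is also a problem at or near the null: at the design effect its probability is Φ(−0.10 / 0.0307), about 0.06%.

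Much of this stands, and it limits what can be said:

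- A reader might infer that no treatment-effect estimate can be had at all. That goes too far, since the risk difference or the risk ratio is recoverable on some readings.
- A reader might take 17% as the trial's type I error. It is conditional. The text implies a fixed control rate by placing the observed value in the response, but it does not say how that value's sampling error is handled.
- A reader might suppose that the same faulty model governs the continuous endpoints. They have a different response, link and distribution, so only the reliance on an intercept without an arm term could carry over.

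The defence does not rescue the text. The protocol subtracts on the response and mentions no offset. The offset reading still gives about 17% if the control rate is fixed. Nor is this detail left to a later plan: the article states the model, and states it wrongly.

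**Conclusion.** The concern holds in this form: the primary model as written is incoherent and must be corrected before analysis. Taken literally, it is undefined at no effect, and its interval cannot cover no effect or harm; these are algebraic facts that need no assumption about the data. On the intervention-only or offset reading a point estimate exists. With the control rate treated as fixed, the standard error is too small by about √2 and two-sided type I error is about 17% instead of 5%. The simulated figures rest on two members per family, 15% loss and ICC 0.20. The documents do not settle which reading is meant.

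The sample size is unaffected. It might be thought to fall with the model, but it reproduces exactly on the ordinary two-arm comparison, which is the analysis that the trial needs.

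**What to change.** Replace the primary-model sentences with the following content:

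- Response: the untransformed 0/1 indicator, for all randomised participants in both arms.
- Model: GEE with randomised arm as a covariate, clustered on family, exchangeable working correlation, robust standard errors, log link with binomial variance. If the log-binomial fit does not converge, use Poisson variance with robust standard errors.
- Effect: the exponentiated arm coefficient with its interval, reported as the risk ratio. An identity-link risk difference is optional; it would match the 10-point difference used for power.
- Time: state how the 12- and 24-month assessments enter the model and which contrast is primary.
- Continuous endpoints: keep their response and identity link, but take the effect from the arm coefficient and not from the intercept. Binary secondary endpoints follow the primary model.

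The cost is a few sentences in the analysis plan. Design, sample size and data collection do not change.

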#### Intervention Part 2. Lifestyle Education (TREATMENT ARM)

Lifestyle education intervention: The lifestyle education component of the treatment arm will include 9–12 nutritional/tobacco/physical activity consultations. All study participants within the selected families in the treatment arm will participate in the lifestyle education component. Within 30 days of study enrolment, all participants will complete culturally specific semi-quantitative food frequency questionnaires (FFQ) and tobacco use surveys. FCHW will receive training from study staff prior to study implementation. Recommended diet modifications for participants will focus on maintaining a healthy weight via redistribution/reduction of calories (by avoiding fried foods and sugar-sweetened beverages), increasing fiber and protein intake via wheat and sprouted pulses, reducing glycaemic load by switching from refined white rice and bread to whole wheat, increasing fruit and vegetable consumption, and reducing salt and sugar intake. Tobacco cessation and strategies to change sedentary behaviour will also be discussed in the nutritional/tobacco/physical activity consultations. Current tobacco users will complete culturally appropriate cessation action guides that identify triggers and action steps to promote tobacco-free behaviours. Strategies to improve physical activity levels of all members of the family will be discussed at least two times during the intervention phase. Family consultations will be repeated every two months to assess dietary, physical activity and tobacco use changes. FCHW workers will also conduct peer-support group education meetings with groups of 10 participants/families once in two months. Support group meetings will review diet modification and tobacco cessation recommendations and highlight peers’ strategies that have led to successful improvements in diet. All individuals with elevated CVD risk factors will be invited to participate in at least 3 such peer-led support groups during the period of the trial.

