#### Care coordination and follow-up

Each family in the treatment arm will be assigned a FCHW. During the intervention phase, FCHW workers will meet with study patients once in two months to assess study progress and participation. In addition, questionnaire data collection and blood draws at home visits after study months 12 and 24 will help to assess detailed attributes of cardiovascular management (FPG, HbA1c, BP, and LDL measures). A mobile phone SMS platform will be used to enhance follow-up. Via SMS, patients will receive study visit reminders and prompts to encourage adherence to treatment and lifestyle goals.

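### Treatment-arm families may share health workers and peer groups, but the GEE and the sample size allow only for within-family correlation, so intervals may be too narrow and power below 90%

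*Protocol article*

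**What the plan says.** The Data analysis plan specifies GEE for the primary endpoint with families as the clusters: "An exchangeable working correlation matrix will be used to incorporate the clustering within the families". A similar GEE approach is to be used for the secondary endpoints. No other level of clustering is mentioned.

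Trial sample size and power uses one correlation, a "rho or intra-cluster correlation coefficient (ICC) of 0.20", with "740 families (370 in each arm) of at least two participants each (minimum of 1480 enrolled participants". The design "will have 90% power to detect an estimated 10% difference in the proportion of participants at 3 or more CHD risk factor goals", that is "55% in the intervention group as compared to the expected rate of 45% in the control group".

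The treatment arm has a grouping above the family:

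- Care coordination and follow-up: "Each family in the treatment arm will be assigned a FCHW". The worker meets participants every two months. The number of families per worker is not given.
- Intervention Part 2: "FCHW workers will also conduct peer-support group education meetings with groups of 10 participants/families once in two months". The same section invites people with elevated risk factors to at least three such meetings.
- The Discussion says the peer sessions are meant to bring support for behaviour change from outside the family.

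The usual care arm has no such grouping after the initial screening, one-time education and referral.

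**The concern.** This is a partially nested design. Families are randomized one by one, but once in the treatment arm they are grouped by worker and, for some members, by peer group. Workers differ in skill and effort, and members of a peer group influence each other by design. Where that makes the intervention more effective for some sets of families than for others, outcomes of families in the same set are correlated.

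The robust variance of a GEE does not repair this. It protects against a wrong correlation structure inside the named cluster, but it takes the clusters, here families, as independent of each other. Positive correlation between treated families makes the treatment-arm standard error too small. Confidence intervals for the primary and secondary effects would then be too narrow, and the trial would have less power than stated.

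The clustering level is not a detail left open. The article fixes it for the analysis and for the sample size, and in both it sits below the level at which the intervention is partly delivered.

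**Working it through.** **Inputs from the protocol article:** 45% v 55%; two-sided alpha 0.05; power 90%; family ICC 0.20; families of two; 15% loss; 370 families (740 participants) per arm.

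**Inputs not in the protocol article, taken as assumptions:** a worker or group ICC, ρ, of 0.01 to 0.05; and *m*, the treated participants per worker or group. Ten participants, or ten families of two, become *m* = 10 × 0.85 = 8.5 or 20 × 0.85 = 17 analysed after loss. The figure of ten is the peer-group size, used only because no caseload is stated.

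**Step 1. Reproduce the plan.**

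Unclustered n per arm = [1.960 × √(2 × 0.5 × 0.5) + 1.282 × √(0.45 × 0.55 + 0.55 × 0.45)]² / 0.10² = 523.3, so 524.

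Family design effect = 1 + (2 − 1) × 0.20 = 1.20, and 524 × 1.20 = 628.8.

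Loss: 628.8 / 0.85 = 739.8, so 740 per arm, or 370 families.

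This matches exactly, so the 90% contains no allowance for worker or peer-group correlation.

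**Step 2. Planned standard error.** With 740 × 0.85 = 629 analysed per arm, SE = √(0.2475 × (1.20 + 1.20) / 629) = 0.0307. Power = Φ(0.10/0.0307 − 1.960) = 90%.

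**Step 3. Add the second level in the treatment arm only.** The treatment-arm design effect becomes DE = 1.20 + (*m* − 2) × ρ. The control arm stays at 1.20.

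- SE ratio for the arm difference: k = √((DE + 1.20) / 2.40)
- Non-coverage of a nominal 95% interval: 2 × (1 − Φ(1.960 / k))
- Power with the correct SE: Φ(0.10 / (0.0307 × k) − 1.960)

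| *m* | ρ | DE | k | Non-coverage | Power |
|---|---|---|---|---|---|
| 2 (one family) | any | 1.20 | 1.00 | 5.0% | 90% |
| 4 (two families) | 0.01 | 1.22 | 1.00 | 5.1% | 90% |
| 4 (two families) | 0.05 | 1.30 | 1.02 | 5.5% | 89% |
| 8.5 | 0.01 | 1.265 | 1.01 | 5.3% | 89% |
| 8.5 | 0.05 | 1.525 | 1.07 | 6.6% | 86% |
| 17 | 0.01 | 1.35 | 1.03 | 5.7% | 88% |
| 17 | 0.05 | 1.95 | 1.15 | 8.7% | 81% |

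Example, *m* = 17 and ρ = 0.05: DE = 1.20 + 15 × 0.05 = 1.95; k = √(3.15 / 2.40) = 1.146; power = Φ(0.10 / 0.0352 − 1.960) = Φ(0.88) = 81%.

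**Step 4. Check of the approximation.** Simulated family means (314 families per arm, 4,000 trials per setting, ten analysed families per group, so *m* = 20) gave error rates of 5.7%, 7.0% and 9.5% at ρ = 0.01, 0.02 and 0.05. The formula gives 5.9%, 6.8% and 9.5%. The simulation gives every worker or group a random effect that averages to zero, so it measures interval coverage. It is not a trial in which the intervention does nothing.

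**The case against.** The strongest reply is that the effect may be small or absent. Nothing states that a worker serves more than one family; sharing is only implied by worker-run groups of ten. Peer groups are aimed at people with elevated risk factors, fixed membership is not stated, and a group need not coincide with one worker's families. Some of the programme does not depend on the worker: screening precedes randomization in both arms, trained staff take the blood pressure measurements, reminders and prompts come by SMS, and linked patients are managed in clinics. All of this stands. It limits the size and certainty of the point, and it is why the result is a range that starts at no error.

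A reader might infer that type I error is inflated. The design does not support that under the strict null. Families are randomized individually, so if the intervention does nothing for anyone, worker skill and group dynamics cannot create correlation in the treatment arm, and a family-level analysis keeps its nominal size. The non-coverage figures apply when effects vary by worker or group.

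Two further objections carry less weight. The calculation is for an ordinary two-arm comparison, whereas the Data analysis plan subtracts the observed control rate and reads the effect from an intercept. That is true, but under that wording nearly all of the reported standard error comes from the treatment arm, so an understatement there would pass through almost in full. It can also be said that provider-level analyses are commonly left to the SAP. That would answer a complaint about missing detail, but here the clustering level is stated.

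**Conclusion.** The point holds in conditional form. The stated model and sample size allow only for correlation within families, while the treatment arm alone has a second grouping that is partly intended to act across families. If effects vary by worker or peer group and workers serve several families, standard errors will be too small, intervals too narrow and power below 90%.

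Under the assumed ICC of 0.01 to 0.05, the standard error of the arm difference is understated by a factor of 1.01 to 1.07 with 8.5 analysed participants per worker or group, and 1.03 to 1.15 with 17. The lowest power in that range is 81%. The calculation applies *m* to every treated participant, so it overstates a pure peer-group effect if only some of them attend. A larger caseload per worker would raise the figures.

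It would be too strong to say that the standard errors are wrong as a matter of fact. The article gives neither the caseload nor the correlation needed for that.

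**What to change.** 1. Record a worker identifier for every treatment family and a peer-group identifier for every attendee, if this is not already done. Membership is easy to log during delivery and hard to reconstruct later.
2. Report the primary and secondary effects with a variance that clusters treatment participants on worker and control participants on family. Family correlation is nested within worker and stays covered. If peer groups mix families of different workers, use the larger connected unit as the cluster.
3. Apply a small-sample correction if workers are few. Ten families per worker, for example, would mean only 370 / 10 = 37 treatment clusters.
4. At the least, prespecify this as a sensitivity analysis beside the family-only model.
5. State the 90% power as before any allowance for worker or peer-group clustering, and give the planned caseload.

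The cost is two identifier fields, a few lines of analysis text, somewhat wider intervals if the correlation is real, and a less favourable stated power. If the correlation is near zero, the intervals should change little.
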